### Data management

Data specified in the trial protocol will be documented in the patient’s digital records. Additional clinical data are available from the electronic patient files. The investigating physician is responsible for appropriate completion of the form. The authors (AS and NS) are responsible for database development, data acquisition, data storage, and validation. Data validation includes controls of completeness, consistency, and plausibility of the data documented in the case report form (CRF) = case report formand electronic dossier using a query system between data management and the investigating physician.

### Adverse events and severe adverse events

The term adverse event (AE) describes any sign, symptom, syndrome, or any disease occurring newly in a trial participant after consent to the trial and being of particular interest for the assessment of the disease or the security of the therapeutic concept. Any AE is documented in the CRF or electronic file of the patient.

For the purposes of this trial the definition of an adverse event will consist of any one of the following:Impairment of the general condition of the patient,Physical injury, including falls,Infection other than wound infection, sepsis or Systemic Inflammatory Response Syndrome (SIRS) Intracranial bleeding in the proximity of the ventricular catheter,Wound infection or dehiscence at the emersion site of the ventricular catheter,Newly occurred neurological deficit,Arterial or venous thrombosis,Any suspicious findings that may have relationship to the study.

For the purposes of this study the definition of a serious adverse event (SAE) will consist of any one of the following:Fatal events or death,Any life-threatening condition,Disabling or incapacitating events,Events that require prolongation of hospitalization,Events that require intervention to prevent permanent impairment.

The relation of the AE or SAE (as a cause or result) to any other AE or SAE will be scored on a two-point scale; 0 - no, 1 - possible (brief description), or 2 - yes (give brief description). The investigator’s estimation of the severity of the problem to the study or study device (to be measured only, if the AE or SAE is or might be related to study) will be measured and scored on a three-point scale; 1 - mild, 2 - severe, or 3 – life-threatening. The investigator’s recommendation to change the protocol, informed consent, or assent form will be given as a binary answer of yes (with a brief description) or no. The outcome of AE or SAE will be assessed until discharge using a four-point scale; 1 - full recovery, 2 - permanent deficit, 3 - not yet fully recovered, or 4 - not known.

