The guiding instrument consists of a base with three pins to be rigidly placed on the bone surface over the burr hole. A semicircular guide rod (Aesculap AG, Tuttlingen, Germany is mounted to the base in which an angle scale is engraved. Within the guide rod, a tube can be individually adjusted in one orientation at different angulations with a range from -60° to 60°. Different tubes are designed with inner diameters of 2, 2.5, and 3 mm in order to guide catheters at different sizes. At the respective angle adjustment, the tube is fixed to the guide rod by a mounting screw. The base is opened at one side to enable the view or insertion of any instrument towards the lower opening of the tube. The guiding tool is positioned parallel to the midline along the engraved linear markings on the base of the instrument. Thereby, a rectangular insertion towards the sagittal convexity and an individual insertion angle towards the coronal tangent at the entry point can be established via the tube.

After opening the dura, once the appropriate trajectory is chosen, a ventricular catheter is inserted according to the pre-calculated insertion angle (for a detailed description see Thomale *et al*.
[20]). After receiving tactile feedback from entering the ventricle, the stylet is removedCerebrospinal fluid (CSF) drainage ensures that the ventricular catheter is correctly in place. Catheters deemed to be suboptimally placed are repositioned when necessary. We rely on length markings on the ventricular catheter and, when possible, flow through the distal catheter to ensure the catheter has not been moved after fixation to the skin and is continuing to provide a conduit for CSF. The remainder of any following shunt procedure or connection to an Ommaya reservoir will be performed using standard techniques.

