The classical freehand technique uses anatomical landmarks and the catheter is placed in the anterior horn of the lateral ventricle through a burr hole just anterior to the coronal suture in the mid-pupillary line (at the level of Kocher’s point; a point on the surface of the cranium 2.5 cm from the midline and 1 cm anterior to the coronal suture, approximately 11.5 cm above the nasion). The target is the ipsilateral frontal horn just anterior to the foramen of Monro to avoid the choroid plexus. The right nondominant side is preferred. The catheter is directed freehand, using external landmarks in the coronal plane towards the ipsilateral medial canthus and in the sagittal plane through the external auditory meatus. A post-procedural CT scan of the brain is performed within 24 hours as part of standard care for postoperative control, or earlier in case of postoperative CSF drainage problems.

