### Outcome assessment

#### Primary outcome measures

The first primary outcome measure will be the frequency and percentage of correct placements of the ventricular catheter, assessed by the three-point scale of Kakarla *et al*., with an additional 1a/1b criteria (Table 
1)
[21]. The effect size will be measured using relative risk, absolute risk reduction, and numbers needed to treat. The second primary outcome measure will be the frequency and percentage of acute ventricular revisions (within one week for an improperly placed catheter). Assessment is performed by an investigator blinded to the study allocation. The effect size will be measured using relative risk, absolute risk reduction, and numbers needed to treat.

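### The adverse event list names bleeding only near the catheter and states no blinded reading for haemorrhage, so ascertainment of bleeding may differ by arm

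*Protocol article*

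**What the plan says.** The section "Intracranial bleeding in the proximity of the ventricular catheter" comes from, Adverse events and severe adverse events, defines an adverse event by a list. This is the only item that names intracranial bleeding, and it gives no distance, imaging time or reader. Three other items could also take in a bleed: impairment of general condition, "Newly occurred neurological deficit", and "Any suspicious findings that may have relationship to the study". The criteria for serious events carry no restriction by site.

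On recording, the same section says "Any AE is documented in the CRF or electronic file of the patient", and Data management says "The investigating physician is responsible for appropriate completion of the form". The investigator rates severity. No blinding is stated for any of these steps.

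On blinding, the Abstract and Design and setting confine it to catheter tip location. Primary outcome measures adds "Assessment is performed by an investigator blinded to the study allocation".

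On imaging, the Abstract defines the primary outcome on a postoperative CT, and the guided technique is planned on a preoperative CT. The freehand paragraph of the surgical technique section adds "A post-procedural CT scan of the brain is performed within 24 hours as part of standard care for postoperative control".

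On use, Secondary outcome measures compares procedure-related and nonsurgical complications at discharge between arms. Interim analyses bases the first stop-point on the primary outcomes and adverse events.

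**The concern.** The named item measures bleeding relative to the catheter, and where the catheter goes, and after how many passes, is what randomisation is meant to alter. The trial's stated hope is fewer passes with the guide. The article also provides for repositioning suboptimal catheters and counts the placements required. If the freehand arm has more abandoned passes, the region around the catheter may capture a different share of its bleeding than in the guided arm. That could happen even with a neutral recorder.

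A second difficulty lies on top of this. For a silent bleed judged not to be near the catheter, entry depends on someone deciding that it may be related to the study, and the article does not say that this person is blinded. Consent procedure notes that about half of patients cannot consent at admission. If many of these patients are neurologically impaired, which is an inference, the route through a new deficit would be less dependable for them.

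At stake are the between-arm comparison of complications and the safety part of the interim look, where event counts will be small.

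**Working it through.** **Figures in the plan.** No stated figure concerns bleeding, so none is in error here. The denominator used below, 118 per arm, is sound: 31% against 15.5% misplacement, two-sided 5%, 80% power and pooled variance give 116 per arm, close to the stated 118.

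**Routes by which a bleed is recorded, set side by side.**

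| Bleed | Route into the record | Depends on |
|---|---|---|
| Near the catheter | Named item | Judgement of nearness; blinding not stated |
| Elsewhere, with symptoms | New deficit, impaired general condition, or a serious-event criterion | Clinical detection |
| Elsewhere, silent | Catch-all item only | Judgement of relatedness; blinding not stated |

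The third row is the weak one. Such bleeds are not excluded, but they are neither named nor systematically sought.

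**Is a blinded read available?** The primary outcome is graded on a postoperative CT by a blinded assessor, so assessing it requires such a scan in both arms. Preoperative CT imaging also exists. A paired read is therefore feasible without new imaging. Only the 24-hour timing in the guided arm has to be inferred, because that sentence sits in the freehand paragraph.

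**Illustration 1: events that depend on judgement (rates assumed).** Let p be the true bleeding risk and q the share away from the catheter. Events per arm = 118 × p × q.
- p = 10%: 118 × 0.10 = 11.8 bleeds.
- q = 30%: 11.8 × 0.30 = 3.5 events.
- q = 10% to 50%: 11.8 × 0.10 = 1.2 to 11.8 × 0.50 = 5.9 events.
- At the interim, 60 per arm: 60 × 0.10 = 6 bleeds, of which 6 × 0.30 = 1.8 lie elsewhere.

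These are counts open to attribution. They are not a bias. If one arm recorded all of the remote bleeds and the other none, the false difference would be p × q = 1, 3 or 5 percentage points for q = 10%, 30% or 50%.

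**Illustration 2: unequal recording (rates assumed).** Suppose the true risk p is equal in both arms, one arm records every bleed, and the other records a fraction s. The spurious difference is p × (1 − s). The last column is the normal-approximation probability of a significant result in that direction (two-sided 5%, 118 per arm). It would be about 2.5% with equal recording.

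| p | s | Spurious difference (points) | Chance of a false significant result |
|---|---|---|---|
| 5% | 75% | 1.25 | 7% |
| 10% | 75% | 2.5 | 10% |
| 20% | 75% | 5.0 | 17% |
| 30% | 75% | 7.5 | 26% |
| 5% | 50% | 2.5 | 17% |
| 10% | 50% | 5.0 | 31% |
| 20% | 50% | 10.0 | 58% |
| 30% | 50% | 15.0 | 79% |

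The 50% rows are deliberately extreme. The table shows how sensitive the comparison would be to unequal recording. It does not show that recording will be unequal.

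**The case against.** The strongest reply is that the list is not closed in effect. New blood on CT after the study procedure fits the catch-all item readily, serious events have no site limit, and the complications outcome is not confined to the adverse event list. This stands: a reader might infer that bleeding away from the catheter is left out, and the article does not support that. The gap is in how such bleeding enters, not in whether it can.

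Four other tempting readings also go beyond the text.
- That the treating physician records events. The article says the investigating physician. The treating physician appears under Randomization. In a single-centre surgical trial it is reasonable to expect that the recorder knows the arm, but this is inferred.
- That only bleeding around the final catheter counts. The item does not say final. With one frontal burr hole, blood at the entry point or along an earlier tract may well be regarded as near the catheter. Since nearness is undefined, this can be argued either way.
- That every patient is said to have a 24-hour CT read blinded. This joins the freehand paragraph to the blinding statement for tip location.
- That bleeding is the trial's key harm. The article ranks no harms.

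Two further points have weight. Limiting bleeding to the catheter region is a defensible choice where trauma or haemorrhagic disease can produce new blood elsewhere. And a working definition or reader instructions may stand in the full protocol or case report form, which is not shown. Missing detail is therefore not the complaint. The point is the restrictive wording that the article does fix, together with blinding that it expressly ties to other outcomes.

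**Conclusion.** The point holds in a limited form. The article names bleeding only in an undefined area around a catheter whose position and passes may differ by arm. It leaves silent bleeding elsewhere to a relatedness judgement with no stated blinding, although the primary outcome already requires a blinded CT read. Ascertainment of bleeding may therefore differ by arm. This is a vulnerability, not demonstrated bias, and its direction is not known.

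Its size cannot be derived from the documents. The figure of about 1 to 6 events per arm rests wholly on an assumed 10% bleeding risk and an assumed 10% to 50% share away from the catheter. No stated figure changes, and the primary tip-location comparison is unaffected. The change is worth making because it is cheap and removes a judgement open to knowledge of the arm.

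**What to change.** On the postoperative CT read already done blinded for tip location, have the same assessor record any new or increased intracranial haemorrhage compared with the preoperative CT:
- present or absent;
- if present, along a catheter tract or at the burr hole, or elsewhere.

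Use this record for the comparison of bleeding by arm, including at the interim look, and report tract-related and other bleeding separately. Leave clinical adverse event reporting as it is.

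The cost is one or two extra fields, with no new scan or reader. There are two drawbacks. More small asymptomatic bleeds will be counted in both arms. Some blood classed as elsewhere will reflect the underlying disease, not the procedure, which is why the two categories should not be merged.

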### Interim analyses

This trial will follow a group sequential design, with two stop-points (interim and final analysis; K = 2). The trial will stop if efficacy rules are met. The endpoints assessed at the first stop-point will be based on primary outcomes and adverse events. The first will be the interim analysis which will occur after the accrual of 60 patients in each arm (120 total), thus representing an information fraction of 0.51 at interim analyses. For the efficacy stop-point the commonly used O’Brien-Fleming approach will be used, and a *P* value of 0.0051 at the interim and 0.0415 at the final analysis will be used
[26].

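### Adverse-event severity is graded only for events judged possibly related to the study, so any table of events by severity would rest on selectively graded events

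*Protocol article*

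**What the plan says.** All of the following is in the Protocol article.

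- **Severity.** The section Adverse events and severe adverse events asks for the investigator's "estimation of the severity of the problem to the study or study device", which "will be measured and scored on a three-point scale; 1 - mild, 2 - severe, or 3 – life-threatening". A parenthesis limits this grading: it is "to be measured only, if the AE or SAE is or might be related to study".
- **Relation.** The only relation scale in that section is about something else: "The relation of the AE or SAE (as a cause or result) to any other AE or SAE will be scored on a two-point scale". Its listed values are 0, 1 and 2.
- **Not subject to the condition.** The same section has every adverse event documented, defines serious events without reference to cause, and scores the outcome of events up to discharge. Secondary outcome measures lists complications by frequency and percentage, covering both procedural and nonsurgical ones.
- **Blinding.** Methods/Design and Design and setting state it for the assessment of catheter tip location, and Primary outcome measures for the assessment of the primary outcomes. It is not stated for adverse events. Under Randomization, the treating physician performs the allocation online. Under Data management, the investigating physician completes the form.
- **Interim.** Interim analyses says: "The endpoints assessed at the first stop-point will be based on primary outcomes and adverse events".

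**The concern.** Whether an event might be related to the study is an opinion, and here that opinion decides whether a severity grade exists at all. If the person forming it knows the arm, events of the same kind may be judged differently. A bleed near the catheter may be linked to the study more readily after use of a new guide than after the standard freehand procedure. An investigator might equally treat both randomized procedures alike, or lean the other way.

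The consequence is missing severity that may depend on the arm. A severity table could then show a difference that is not there, or hide one that is. Adverse events are looked at both at the interim and at the end, so such a table could be drawn up at either point. This is a rule the document states, not a detail left to an analysis plan. If the case report form has a field for relatedness to the study, that would record the filter, but it would not supply grades for the events filtered out.

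**Working it through.** The plan gives no figure on this point, so there is none to reproduce. The check is a reading of the text, followed by an illustration with assumed inputs.

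**Step 1: which safety data carry the relatedness condition.**

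| Item | Section | Conditional on relatedness to the study? |
|---|---|---|
| Documentation of adverse events | Adverse events and severe adverse events | No, except that one listed event type (suspicious findings) refers to a possible relation to the study |
| Classification as serious | same | No |
| Outcome of the event | same | No |
| Complication frequency | Secondary outcome measures | No |
| Severity grade | same as first row | Yes |

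The effect is therefore confined to severity.

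**Step 2: what the condition refers to.** The condition concerns relation to the study. The study device appears only in the description of what is graded. Freehand placement is one of the two randomized procedures, so a freehand event can also satisfy the condition. The rule is worded identically for both arms; only its application can differ.

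**Step 3: how selective grading would act.** Let p be the true risk of a severe event and g the share of severe events judged possibly related, in the guided (G) and freehand (F) arms. The expected number graded severe is n × p × g, so with equal n

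observed ratio = (p_G / p_F) × (g_G / g_F).

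The bias factor is g_G / g_F and does not depend on p.

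**Step 4: illustration.** n = 118 per arm comes from Sample size analysis. The true risk of 10% in both arms and all values of g are assumptions. Expected severe events per arm: 118 × 0.10 = 11.8.

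| g_G | g_F | Graded severe, guided | Graded severe, freehand | Apparent ratio |
|---|---|---|---|---|
| 1.0 | 1.0 | 11.8 | 11.8 | 1.0 |
| 0.9 | 0.6 | 11.8 × 0.9 = 10.6 | 11.8 × 0.6 = 7.1 | 0.9 / 0.6 = 1.5 |
| 0.9 | 0.3 | 10.6 | 11.8 × 0.3 = 3.5 | 0.9 / 0.3 = 3.0 |
| 0.6 | 0.9 | 7.1 | 10.6 | 0.6 / 0.9 = 0.67 |

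With a 15% risk, 118 × 0.15 = 17.7 severe events per arm. Shares of 70% and 30% then give 12.4 against 5.3 (ratio 2.3), and 70% against 50% gives a ratio of 1.4. Whenever the shares are equal, the ratio is 1.0. In every row, the ratios for serious events and for complication frequency stay at 1.0, because those data do not pass through the filter.

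The table shows the mechanism only. Nothing in the document says what the shares would be.

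**The case against.** The strongest case against runs as follows. The rule is the same in both arms. The listed between-arm safety outcome is complication frequency, not severity, and no comparison by severity grade is specified. The gravest events are captured whatever the attribution: the top severity grade, life-threatening, is also a criterion for a serious event, and those criteria carry no relatedness condition. The interim text mentions adverse events but not their severity, and the only stopping rule stated is for efficacy. The size of any bias is wholly assumed.

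Most of this stands and sets the limits of the point. What is lost is chiefly the mild or severe grade of events judged unrelated. The serious-event criteria soften the loss, and grading afterwards from records may be possible, though it would be weaker. What does not fall is that following the rule leaves severity selectively missing.

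A reader might infer more in three ways:

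- **That the whole safety comparison is asymmetric.** The first table under the working rules this out: severity is the only item filtered.
- **That freehand events fall outside grading because that arm has no study device.** The condition names the study, not the device.
- **That the assessor is unblinded and that relatedness is never recorded.** Knowledge of the arm is a reasonable inference from who randomizes and where blinding is stated, but the document does not say who grades events. The case report form is not shown and may contain a relatedness field.

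**Conclusion.** The point holds in a narrow form. Severity is graded conditionally on a judgement of relatedness to the study, made by someone not stated to be blinded. Any tabulation of events by severity between arms, at the interim or at the end, would rest on selectively graded events. The bias could go in either direction, by an amount the document does not allow one to estimate; ratios such as 1.5 or 3.0 reflect the chosen inputs and are not predictions. The conclusion assumes that the investigator probably knows the arm and that someone will look at severity by arm; the document states neither. It is a cheap improvement to the safety data, not a flaw in the primary comparison.

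Separately, a scale described as having two points lists three values. That is a clerical correction only.

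**What to change.** - Delete the relatedness condition and grade severity for every adverse event and serious adverse event in both arms.
- Record relation to the ventriculostomy procedure in both arms, and relation to the guide in the guided arm, as an item separate from severity. If the case report form already holds such an item, cite it in the protocol.
- Present events by severity regardless of attribution, with events judged related as a secondary table.
- Correct the label of the scale for relation to other events so that it matches its three values.

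The cost is a short protocol change, one or two fields on the form and slightly more form-filling per event. It is best done before enrolment, because grades assigned afterwards from records are weaker than grades assigned at the time.

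### The outcome scale for adverse events has no category for death, although death is the first listed criterion for a serious adverse event

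*Protocol article*

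**What the plan says.** The section of the protocol article on adverse and severe adverse events does three things that bear on this point.

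- It defines a serious adverse event by any one of five criteria. The first is "Fatal events or death".
- It sets the outcome rule and its window: "The outcome of AE or SAE will be assessed until discharge using a four-point scale". The levels follow in the same sentence: "four-point scale; 1 - full recovery, 2 - permanent deficit, 3 - not yet fully recovered, or 4 - not known".
- It gives two neighbouring scales. Severity is scored only when the event is or might be related to the study, and its highest level is "3 – life-threatening". The relation of one event to another is "scored on a two-point scale; 0 - no, 1 - possible (brief description), or 2 - yes".

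The section on interim analyses says of the look at 120 patients: "The endpoints assessed at the first stop-point will be based on primary outcomes and adverse events". It does not say which adverse event fields will be reviewed.

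**The concern.** A closed code list should have a correct value for every event it has to score. Here the list is applied to all serious adverse events, and the first kind of serious event that the section names has no correct value. Whoever completes the form for a patient who dies before discharge, for example after a bleed near the catheter, must pick a code that is untrue or leave the field empty.

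What is at stake is the summary of harm by arm. A table of event outcomes built from this field would have no row for death. The deaths would sit with disabled survivors, with patients still recovering, with unknown outcomes or among missing values, possibly with different choices for different patients. The situation is foreseeable. The consent section says that the procedure is often done in an emergency and that about half of the patients cannot consent at admission, and the outcome window covers the whole hospital stay.

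**Working it through.** No arithmetic beyond counting levels applies. All inputs come from the adverse events section unless stated otherwise.

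**Step 1. Is the list complete as printed?** A level could have been lost in condensing or extracting the text, so compare the announced number of levels with the listed number.

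| Scale | Levels announced | Levels listed | Levels for a fatal event |
|---|---|---|---|
| Outcome | 4 | 4 (codes 1 to 4) | 0 |
| Severity, if possibly study-related | 3 | 3 (codes 1 to 3) | 0 |
| Relation to another event | 2 | 3 (codes 0, 1, 2) | not applicable |

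For the outcome scale the two counts agree, so the list is whole. The absence of death is what the article states and not a detail left to a fuller document. For the relation scale the counts differ by one. All three codes are labelled, so only the scale's name is wrong.

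**Step 2. Must the scale be applied to deaths?** It covers adverse and serious adverse events without exception. Death is a criterion for a serious adverse event. The scoring period runs to discharge, so deaths in hospital fall within it. The answer is yes.

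**Step 3. Does any listed code fit a death?**

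- Code 1, full recovery: false.
- Code 2, permanent deficit: describes a survivor.
- Code 3, not yet fully recovered: implies that recovery is still open.
- Code 4, not known: false, because the outcome is known.
- Empty field: no code is given, and the completeness check promised in the data management section would query it.

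None fits. The article gives no rule for choosing among them.

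**Step 4. What does a table by this field show?** Let an arm have *k* fatal events. With a death code, the table shows *k* under death. With the present codes it shows 0 deaths, and the *k* events are spread over the existing codes and missing values in a way the article does not determine. This holds for any *k* of 1 or more, so no assumed mortality is needed. The article gives none.

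**Step 5. Can a death be found elsewhere?** Yes. It qualifies as a serious adverse event under the fatal criterion, and every event is documented in the case report form or the electronic patient file. One reservation: a serious event is defined by any one of five criteria, and the article does not say that the qualifying criterion is stored as its own field. The bare fact that an event was serious does not separate a death from a prolonged hospital stay.

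**The case against.** The strongest defence is that nothing is lost. Death is itself a criterion for a serious adverse event, so each death enters the safety data whatever its outcome code. The data management section provides for checks and queries against the patient's electronic record. The trial has one centre with its own data management, so deaths by arm can be counted. No planned comparison uses the outcome code: the secondary outcome is the frequency and percentage of complications at discharge, and the only stated stopping rule is for efficacy. Most of this stands, and it limits the point to a fault in one field. It does not make the field correct, because the plan still prescribes a score that cannot be given truthfully for a fatal event.

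A reader might infer more than the documents support.

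- *That deaths must be coded as permanent deficit or as not known.* The article has no rule for coding a death. Code 3 or a blank is equally possible.
- *That deaths would be hidden from the interim review.* The interim section refers to adverse events in general and does not say that the outcome code is what is reviewed. Deaths remain identifiable as serious events.
- *That the size can be expressed as a number of miscoded patients.* That would need an in-hospital mortality, and the article offers no basis for one. Such a number would also count deaths, not deaths lost to analysis.
- *That the severity scale needs a fatal level too.* Severity is a separate field, scored only for events that are or might be study-related. Once the outcome field has a death code, a fatal severity level would largely record the same fact twice.

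**Conclusion.** Wrong as written, and minor. The outcome scale contradicts the definition of serious events in its own section: it must be applied to fatal events and has no level for them. As a result the outcome field cannot correctly record a death, and any tabulation by that field would show no deaths or would mix them with other categories.

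The effect stops there. Sample size, alpha, the primary analysis and the stated comparisons do not depend on this code. The conclusion rests on the printed list being the list that will be used, which the matching count of four supports, and on the scale applying to every serious adverse event, which the text says outright. It needs no assumption about how many patients die: a single death before discharge is enough to expose the fault.

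The mismatch between the name of the relation scale and its three codes is a clerical slip. It does not affect how deaths are recorded.

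**What to change.** - Add death as a fifth outcome code and call the scale five-point.
- Tabulate deaths by arm alongside the adverse events at the interim and final analyses.
- While editing the section, change two-point to three-point for the relation scale.

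The cost is one entry in a code list and one or two sentences in the protocol. There is no added burden on patients and no change to the design. It is best done before data collection starts, because recoding later would mean going back to the patient files for each fatal event.
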